## Abstract

**Background:**

Regional anesthesia is widely regarded as one of the safest anesthetic techniques, yet serious complications—such as nerve injury, hematoma, pneumothorax, and local anesthetic systemic toxicity (LAST)—continue to be reported. Their true incidence remains uncertain, as available data are often derived from registry or retrospective studies with heterogeneous definitions and limited sample sizes. Moreover, the mechanisms underlying complications such as nerve injury are incompletely understood and may extend beyond direct mechanical trauma to include factors such as sub-perineural injection, hematoma formation, altered coagulation, and patient-specific vulnerability.

**Methods:**

The *NEURAL* study, promoted by the Italian Society of Anesthesia, Analgesia and Critical Care (SIAARTI), is a multicenter, prospective, observational study designed to determine the incidence and risk factors for complications following single-shot regional anesthesia of the upper limb, lower limb, and fascial plane. The primary endpoint is the composite incidence of nerve injury, hematoma, pneumothorax, and LAST. Secondary objectives include determining the individual incidence of each complication and identifying patient- and procedure-related risk factors. Data will be collected via the REDCap® (Research Electronic Data Capture) platform from more than 40 Italian centers. Standardized follow-up will be performed at 24 and 48 hours, 15 and 30 days, and monthly thereafter for unresolved neurological deficits, up to one year. Statistical analyses will include logistic regression modeling to identify independent predictors of complications.

**Expected results:**

Based on an estimated complication rate of 0.5%, a minimum of 3,396 patients will be required to ensure adequate precision of incidence estimates. Nationwide participation is expected to exceed this target.

**Conclusions:**

The *NEURAL* study will provide robust, prospective, and standardized data on complications of regional anesthesia. By identifying their true incidence and modifiable risk factors, the findings are expected to inform safer clinical practice, enhance patient counseling, and support the development of updated evidence-based guidelines.

## Introduction

Regional anesthesia has an extremely high safety profile [1]. However, complications related to regional techniques are reported in the literature such as local anesthetic toxicity, hematoma requiring medical attention or nerve injury [2–4]. Given that such complications are extremely rare their incidence is not fully known, mainly because it is estimated based on registry studies with an often limited sample size.

Moreover, while the cause-effect mechanism of regional anesthesia is clear for some complications – for instance, a pneumothorax following a paravertebral block –, the mechanism of action for other complications, such as nerve injury after regional anesthesia, is not well understood. Historically, it was believed that nerve injury resulted from the needle coming into direct contact with the nerve fibers, essentially causing mechanical trauma. Nevertheless, recent evidence challenges this view, showing that it is mechanically difficult to cause nerve injury solely through direct contact. In fact, nerve damage can occur even without any direct interaction with the nerve [5].

Thus, in addition to factors like local anesthetic toxicity, sub-perineural injection, high injection pressures within the epineurium, and sub-epineural hematoma resulting from forced contact between the needle and the nerve, other contributing factors may also play a role in nerve damage. These include altered coagulation profiles, the patient’s intrinsic fragility, possible comorbidities, and other currently unidentified factors [6].

The aim of the NEURAL study will be to provide a comprehensive estimate of the incidence of complications following regional anesthesia, with particular attention to nerve injury, hematoma, pneumothorax, and local anesthetic systemic toxicity (LAST). Moreover, by conducting a large multicenter prospective observational study, we will also seek to identify patient- and procedure-related risk factors that may predispose individuals to neurological or systemic adverse events. We hypothesize that the true incidence of complications is higher than currently appreciated from registry data, and that specific risk factors—including comorbidities, anticoagulant use, and technical variables related to block performance—contribute significantly to their occurrence.

## Materials and methods

We are reporting the study protocol for the NEURAL study. The study had not yet started at the time of this protocol’s submission to the journal. It is tentatively scheduled to begin in January 2026 and to run for two consecutive years (until January 2028). Study results are expected to be definitive at the end of 2028. The final start date will be updated on ClinicalTrials.gov as soon as it is confirmed.

### Study design and objectives

This protocol has been prepared with the support of the SPIRIT checklist (see S1 File). The NEURAL study, promoted by the Italian Society of Anesthesia, Analgesia and Critical Care (SIAARTI), is a multicenter, prospective observational study designed to investigate the prevalence of complications associated with regional anesthesia of the upper limb, lower limb, and fascial plane blocks.

The primary objective of the NEURAL study is to determine the overall incidence of complications following regional anesthesia, expressed as a composite outcome. This composite outcome will include nerve injury, hematoma, pneumothorax, and LAST, calculated as the total number of complication events divided by the total number of procedures.

The secondary objectives are to determine the incidence of each individual complication (nerve injury, hematoma, pneumothorax, and LAST for each type of regional anesthesia technique. These include upper limb blocks, lower limb blocks, and fascial plane blocks (Table 1), with outcomes calculated as the number of events relative to the total number of procedures performed. In addition, the study seeks to identify risk factors associated with complications following upper limb regional anesthesia, lower limb regional anesthesia, and fascial plane blocks, thereby contributing to a more precise understanding of patient- and procedure-related variables influencing safety in regional anesthesia as described in the relevant paragraph below..

**Table 1 pone.0348493.t001:** Fascial plane regional anesthesia: The most recent nomenclature of the European Society of Regional Anaesthesia (ESRA) [7] will be used. The following blocks will be considered.

Upper limb blocks	Lower limb blocks	Fascial blocks
Interscalene BP block Superior trunk block Supraclavicular BP block InfraclavicularBP block Infraclavicular BP block (coracoid approach) Infraclavicular BP block (retroclavicular approach) Infraclavicular BP block (costoclavicular approach) Suprascapular nerve block (anterior approach) Suprascapular nerve block (posterior approach) Axillary BP block Superficial cervical plexus block Intermediate cervical plexus block Deep cervical plexus block.	Lumbar plexus block Sacral plexus block Fascia iliaca block (suprainguinal approach) Fascia iliaca block (infrainguinal approach) Adductor canal block PENG block Femoral nerve block Femoral triangle block Sciatic nerve block (anterior approach) Sciatic nerve block (transgluteal approach) Sciatic nerve block (infragluteal approach) Sciatic nerve block at the popliteal fossa Nerve to vastus medialis block Genicular nerves block IPACK Common peroneal nerve block Ankle block Pudendal nerve block.	Rectus sheath block Ilioinguinal iliohypogastric nerves block TA block Midaxillary TAP block Subcostal transversus abdominis plane block ESP block Deep SAP block Superficial SAP block TFP block Rhomboid intercostal plane block Retrolaminar block Anterior QLB Lateral QLB Posterior QLB Paravertebral block ITP block Superficial PIP block DeepPIP block; PSP block IPP block

BP:brachial plexus; ESP: Erector spinae plane; IPACK: Infiltration between the popliteal artery and capsule of the knee; IPP: Interpectoral plane;ITP: Intertransverse process; PENG: Pericapsular Nerve Group; PIP: parasternal intercostal plane; PSP: Pectoserratus plane; QLB: quadratus lumborum block; SAP: serratus anterior plane; TAP:Transversus abdominis plane; TFP: Transversalis fascia plane.

The regional anesthesia techniques will be categorized using the most recent nomenclature proposed by the European Society of Regional Anesthesia (ESRA) [6–7] as shown in Table 1

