### Statistical analysis

Data for each continuous variable will be analyzed to assess the normality of distribution using the Shapiro-Wilk test. Continuous variables with normal distributions will be reported as mean (standard deviation); those with non-normal distributions will be reported as median and interquartile range. Analysis of normally and non-normally distributed data will be performed using the two-tailed Student’s t-test and the Mann-Whitney U test, respectively.

If the proportion of missing data exceeds 5% for key variables, multiple imputation by chained equations will be performed under the assumption of missing at random. Imputation models will include all variables used in the primary analyses, including outcomes and relevant predictors. Sensitivity analyses will be conducted to compare complete-case analyses with imputed datasets. In addition, if differential loss to follow-up is observed, inverse probability weighting methods may be applied to assess the robustness of the findings. The amount of missing data and the methods used to address it will be transparently reported according to STROBE recommendations.

Results for categorical variables will be reported as numbers (percentages) and compared between groups using the chi-squared test or Fisher’s exact test, as appropriate.

To determine the strength and direction of association between two variables, the Bravais-Pearson correlation test will be used for variables with a normal distribution, and the Spearman rank correlation test for variables not meeting normal distribution assumptions.

To determine the relationships between the dependent categorical variable (e.g., complications) and one or more independent categorical variables (i.e., complication predictors), logistic regression will be performed to calculate odds ratios (OR) with 95% confidence intervals (CI). Given the anticipated low incidence of complications, rare-event bias may affect conventional maximum likelihood estimation. Therefore, penalized likelihood approaches—such as Firth’s bias-reduced logistic regression—will be used when appropriate to improve the stability and validity of parameter estimates. In cases of extremely sparse data, exact logistic regression methods may also be considered. Model adequacy will be assessed using goodness-of-fit statistics and calibration plots. The presence of multicollinearity will be assessed using variance inflation factors.

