#### Accounting for center-level clustering.

Given the multicenter design of the NEURAL study, patients are clustered within participating institutions, and outcomes may be correlated due to shared clinical practices, operator expertise, equipment, or local protocols. To account for this hierarchical structure, multilevel (mixed-effects) regression models will be used for the primary and secondary analyses. Specifically, random-intercept logistic regression models will be applied to account for between-center variability when estimating associations between predictors and complications. The intraclass correlation coefficient (ICC) will be calculated to quantify the degree of clustering. As a sensitivity analysis, generalized estimating equations (GEE) with robust standard errors will also be considered.

All statistical analyses will be performed using R software. P-values < 0.05 will be considered indicative of statistical significance.

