### Sample size calculation

This is an observational study aimed at investigating very rare complications, the incidence of which is difficult to estimate. Literature reports an incidence ranging from 0 to 2.8%, depending on the study and cohort considered [8].

The sample size estimation was performed using an approach based on the precision of the proportion estimate, defined as the total width of the confidence interval. For this purpose, the Agresti-Coull Wilson method was applied [9].

Starting from a cumulative incidence of 0.005 (0.5%) [10], with a 95% confidence level and aiming for a confidence interval width of 0.003, a minimum of 3,396 subjects must be enrolled. The estimation was conducted using the {presize} package of R software, version 4.3.3 (2024-02-29 ucrt).

When the study was initially planned, we anticipated enrolling at least 10 centers in the NEURAL study, with an expected average recruitment of approximately 350 patients per center over two years, making the achievement of the planned sample size a realistic goal.

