### Strengths and limitations

A key strength of the NEURAL study lies in its multicenter, prospective, and observational design, coordinated under the auspices of SIAARTI. The inclusion of multiple tertiary centers across Italy ensures broad representation of clinical practice, patient demographics, and procedural variability, thereby enhancing the generalizability of results.

The study’s standardized definitions of complications and structured follow-up at 24 and 48 hours, as well as at 15 and 30 days—with extended follow-up up to one year for nerve injury—will enable accurate detection of both early and delayed complications. The detailed recording of procedural variables (e.g., ultrasound guidance, injection pressure, adjuvants used) and patient characteristics (e.g., comorbidities, anticoagulant use) allows for in-depth risk factor analysis using multivariable modeling.

However, the study also has inherent limitations. As an observational protocol, it cannot establish causal relationships between regional anesthesia and complications. Additionally, the identification of rare events may still be constrained by the sample size, despite careful power calculation. Potential variability in operator experience and institutional practices may introduce confounding, though standardized definitions and training across centers are intended to minimize this effect.

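### About 17 expected events support only a few adjusted parameters, the penalised and random-intercept models are not reconciled, and operator experience is not among the registered data

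*Protocol article*

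**What the plan says.** In the protocol article, Study design and objectives states that "the study seeks to identify risk factors associated with complications following upper limb regional anesthesia, lower limb regional anesthesia, and fascial plane blocks". The Methods paragraph of the abstract says that logistic regression will identify independent predictors. Strengths and limitations promises in-depth risk-factor work by multivariable modeling.

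Statistical analysis relates complications to "one or more independent categorical variables (i.e., complication predictors), logistic regression will be performed". It warns that rare events bias ordinary maximum likelihood and says that penalised methods such as Firth's will be used when appropriate. For extremely sparse data, "exact logistic regression methods may also be considered".

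Accounting for center-level clustering says that mixed-effects models will serve the primary and secondary analyses, and that "random-intercept logistic regression models will be applied to account for between-center variability when estimating associations between predictors and complications". It adds that the intraclass correlation coefficient (ICC) will be calculated.

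Sample size calculation gives a precision argument for one proportion and concludes that "a minimum of 3,396 subjects must be enrolled". It gives no event count, effect size or power for the risk-factor objective, yet Strengths and limitations says that "the identification of rare events may still be constrained by the sample size, despite careful power calculation".

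The same section states: "Potential variability in operator experience and institutional practices may introduce confounding". The list of data to be registered (under Data collection and Intraoperative time) contains no item on the operator.

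**The concern.** The number of parameters that a logistic model can carry depends on the number of events, not the number of patients. With a rare composite, a sample chosen for the precision of one proportion may yield too few events for adjusted odds ratios. These would then be unstable, or would depend heavily on which predictors happened to be selected. A statement that independent or modifiable risk factors had been identified would go beyond the data.

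Two features of the plan add to this. The section that recognises rare-event bias and the section that prescribes the clustered model do not refer to each other, so the reported model could lack the penalisation that the article itself considers necessary. And a confounder that is not recorded at enrollment cannot be adjusted for later, whatever a subsequent analysis plan says.

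**Working it through.** **Inputs from the article.** Minimum N = 3,396, incidence 0.005, 95% confidence, target total interval width 0.003 and about 350 patients per center over two years (Sample size calculation). Three block regions (Study design and objectives). 43 centers (Recruitment) or 46 (Ethical approval and protocol registration). Six months of recruitment per center (Study duration). Significance at 0.05.

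**Assumptions.** Equal regions, equal centers, a binary predictor with 10% to 50% exposure, and 5 to 10 events per adjusted parameter as a rough guide.

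**1. The plan's own figure.** The Agresti-Coull width is 2z√[p̃(1−p̃)/ñ], with ñ = n + z² and p̃ = (np + z²/2)/ñ. At n = 3,396, ñ = 3,399.8 and p̃ = 0.00556, so the width is 0.0050. A width of 0.003 needs n = 8,853. The stated N therefore fits a width of 0.005, not 0.003. That is a separate point, but both values of N are carried below.

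**2. Expected events.** 3,396 × 0.005 = 16.98, about 17 (95% binomial range 9 to 25). Per region: 16.98/3 = 5.7.

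**3. Adjusted parameters.** 17/10 = 1.7 and 17/5 = 3.4, so about 2 to 3 parameters pooled. Within one region, 5.7/5 = 1.1, so about one at most.

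**4. Other scenarios.**

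| Scenario | Patients | Events | Per region |
|---|---|---|---|
| Planned minimum | 3,396 | 17 | 5.7 |
| 350 per two years prorated to six months (87.5 per center), 43 to 46 centers | 3,763 to 4,025 | 19 to 20 | 6.3 to 6.7 |
| N needed for width 0.003 | 8,853 | 44 | 15 |
| 43 centers with 350 patients each | 15,050 | 75 | 25 |
| Planned minimum at 2.8%, the top of the cited range | 3,396 | 95 | 32 |

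The prorated row follows from the article's own recruitment rate and window, and barely changes the count.

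**5. Power for one binary predictor, unadjusted.** With exposure share π and odds ratio OR, the risk p₀ in the unexposed solves (1−π)p₀ + πp₁ = 0.005, where p₁ = OR·p₀/(1−p₀+OR·p₀). For π = 0.3 and OR 4, p₀ = 0.00264 and p₁ = 0.0105. Power is the simulated share of 2×2 tables (0.5 added to each cell) in which the log odds ratio has |z| > 1.96.

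| N | Exposure | OR 2 | OR 3 | OR 4 |
|---|---|---|---|---|
| 3,396 | 10% | 29% | 54% | 73% |
| 3,396 | 30% | 30% | 61% | 80% |
| 3,396 | 50% | 21% | 47% | 65% |
| 1,132 (one region) | 30% | 10% | 21% | 30% |

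Fisher's exact test at 20% exposure is somewhat lower: 25%, 54% and 75% pooled. Adjustment and clustering will generally lower these figures further.

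**6. Centers without an event.** With 3,396/43 = 79 patients per center, P(no event) = 0.995^79 = 0.67, so about 29 of 43 centers have none. With 46 centers it is about 32. The center variance and the ICC would rest on the remaining third.

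**7. The two model statements.** Statistical analysis gives a reason to penalise. Accounting for center-level clustering prescribes a random intercept for the primary and secondary analyses and mentions neither an estimator nor a penalty. An ordinary random-intercept fit carries no Firth penalty. The text does not say which model supplies the reported odds ratios.

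**The case against.** The strongest reply is that the article already acknowledges sparsity. It names Firth and exact methods, calls all secondary analyses hypothesis-generating, puts intervals ahead of p-values and concedes that sample size may limit the work. It also treats 3,396 as a minimum that it expects to exceed. This is largely fair and is why the point is not graver. But penalisation reduces bias without adding information, the prorated recruitment adds only two or three events, and the hypothesis-generating label sits badly with a promise of independent predictors.

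A second reply is that predictor selection and the joining of penalisation with clustering belong in an analysis plan. Leaving out a predictor list is indeed no fault. What remains is two printed prescriptions that do not meet, and a claim that the expected events do not support.

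Several stronger readings are tempting, and the text does not support them:
- That risk factors cannot be identified at all. Pooled unadjusted power of about 80% at an odds ratio of 4 contradicts this. The problem is low power and little room for adjustment.
- That three separate models are prescribed. The objective names three regions, but no section specifies a model for each, and a pooled model is compatible with the text.
- That every recorded item, about 28 by count, enters one model. The list describes data collection, so a ratio of events to those items has no basis in the plan.
- That 43 centers cost 43 parameters. A random intercept costs one variance parameter.
- That an exact model would condition on center and discard event-free centers, or that age, BMI and dose will be cut into groups. Neither is stated, although predictors are described as categorical.

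On operator experience, the article counts operator expertise among the sources of center-level correlation, so the random intercept takes up part of it, and it relies on training across centers. Differences between operators within a center remain.

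**Conclusion.** The point holds as a moderate one on a secondary objective. At the planned minimum, about 17 events allow roughly 2 to 3 adjusted parameters pooled. Only very strong predictors are detectable, and adjusted analyses within a region are not supportable. The penalised and random-intercept prescriptions need to be reconciled, and the center variance and ICC would be poorly estimated. Operator experience is named as a confounder but not listed for collection.

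The sizes rest on 0.5% incidence, equal regions and centers, 10% to 50% exposure and the rough guide of 5 to 10 events per parameter. With 75 to 95 events, a short adjusted pooled model would be reasonable (75/10 = 7.5 to 95/10 = 9.5 parameters), but each region would still have only 25 to 32. The full collection form is not shown. If it already records operator experience, that part reduces to a correction of the article's list.

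**What to change.** - Make the risk-factor analysis one pooled logistic model of the composite, Firth-penalised or a penalised mixed model, with block region as a covariate.
- Prespecify a short, ordered predictor list and a limit tied to the observed event count. Block region takes two parameters, so at 17 events there is room for about one further predictor; more enter only if events accrue.
- Keep continuous predictors continuous.
- State one method for clustering: a center bootstrap with the Firth model, or the random intercept of the penalised mixed model. Report the ICC with its interval, as imprecise.
- Report region-specific results and all other predictors descriptively.
- Add one operator-experience field to the form before enrollment. This part is urgent, because it cannot be recovered later.
- State the expected events and the detectable odds ratio, limit the independent-predictors claim accordingly, and describe the sample size as a precision calculation rather than a power calculation.

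The cost is analysis-plan wording, one extra form field with any amendment it requires, fewer adjusted predictors and a more modest claim.
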